## Abstract

**Background:**

Having a ‘theory of mind’, or having the ability to attribute mental states to oneself or others, is considered one of the most central domains of impairment among children with an autism spectrum disorder (ASD). Many interventions focus on improving theory of mind skills in children with ASD. Nonetheless, the empirical evidence for the effect of these interventions is limited. The main goal of this study is to examine the effectiveness of a short theory of mind intervention for children with ASD. A second objective is to determine which subgroups within the autism spectrum profit most from the intervention.

**Methods:**

This study is a randomized controlled trial. One hundred children with ASD, aged 7 to 12 years will be randomly assigned to an intervention or a waiting list control group. Outcome measures include the completion of theory of mind and emotion understanding tasks, and parent and teacher questionnaires on children’s social skills. Follow-up data for the intervention group will be collected 6 months after the interventions.

**Discussion:**

This study evaluates the efficacy of a theory of mind intervention for children with ASD. Hypotheses, strengths, and limitations of the study are discussed.

**Trial registration:**

Netherlands Trial Register NTR2327

## Background

With a recently estimated prevalence of 1 in 88 children (1 in 54 boys) [1], autism spectrum disorders (ASD) are common and lifelong neurodevelopmental disorders, defined by a triad of impairments in social reciprocity, (non-) verbal communication and restricted and repetitive behaviors [2]. A core deficit in individuals with ASD is their limited perspective-taking, or ‘theory of mind’, ability. ‘Theory of mind’ (ToM) refers to having the ability to attribute mental states, such as intentions, beliefs, desires, and emotions, to oneself and to other people [3]. While a great many studies have shown a deficient ToM in children with ASD [4,5], it has also been shown that some individuals with ASD do develop ToM skills, albeit in a delayed fashion [6]. Whether deficient or delayed, limited ToM skills seriously impair everyday social interactions. This study examines the effectiveness of a ToM treatment in children with ASD.

Many interventions have focused on social skill development in individuals with ASD [7], with various interventions specifically focusing on ToM [8-12]. However, the empirical evidence for the effectiveness of these interventions is limited and inconclusive [13], and many studies were hampered by small samples, absence of randomized controlled trials (RCTs), and outcome measurements lacking sensitivity [14]. To date, only two RCTs have targeted the effect of ToM-focused interventions in children with ASD. First, Fisher and Happé [10,15] studied the effectiveness of the ‘picture-in-the-head’ training method in 27 children, aged 6 to 15 years, with ASD with varying cognitive abilities. This 5 to 10 day individual intervention showed increased ToM understanding in an intervention group compared with a control group, even at follow-up periods of between 6 and 12 weeks later, but no differences were found for teacher-reported ToM in everyday life. Second, Begeer *et al.*[12] studied 40 children aged 8 to 13 years with ASD without cognitive delay (IQ of 70 or above). Participants took part in a group intervention, including 16 one-hour sessions. Parents were involved to stimulate generalization of the trained skills. The intervention improved children’s understanding of beliefs, false beliefs, mixed emotions, and complex emotions. However, no impact was found on self-reported empathy or parent-reported social behavior. Both RCTs showed modest effects of the ToM intervention on conceptual understanding of ToM, whereas no results were found on practical social behavior skills as reported by parents and teachers.

These intervention studies are limited for various reasons. The sample sizes are relatively small (27 and 40 participants, respectively), resulting in insufficient power to detect subtle treatment effects. Furthermore, children with ASD may vary widely in IQ, social interaction style [16,17], the severity of the disorder [18] and comorbidity [19]. These factors may influence the impact of the intervention. In addition, previously used social skills questionnaires [10,15] focused on broad domains of behavioral inclinations (for example, the Children’s Social Behavior Questionnaire (CSBQ) [20]; the Theory of Mind and Executive Function Questionnaire [15]). It is likely that this decreased the sensitivity to subtle behavioral changes. Examining the occurrence of explicit treatment-related behavior over a limited time (for example, one week) may improve the detection of behavioral change. Finally, previous studies included either parent or teacher informants, but never both in the same study, thus ignoring different levels of structure in school or home environments, which may demand specific social skills from children.

In this RCT, we examine the effectiveness of a theory of mind intervention in children with ASD and normal IQ, improving our previous study [12] on six domains (Figure 1): (1) the intervention is shortened (8 instead of 16 sessions), and (2) a larger sample is included in the trial (100 rather than 40 participants), (3) moderating and mediating variables are studied by examining the influence of social interaction style [17] and disruptive behavior [19,21] on the effect of the intervention, controlling for intellectual abilities, (4) a larger range of informants, including children, parents, and teachers, is examined with (5) more sensitive outcome measures, and (6) the persistence of the treatment effects is studied after a period of 6 months.

**Figure 1 F1:**
[figure not shown]
Different stages of the research procedure.

## Methods

### Study design

The study is a randomized controlled trial. There are two groups: an intervention group and a waiting list control group. The Medical Ethics Committee of the VU University Medical Center has approved the project (project no. 2010/241).

### Inclusion and exclusion criteria

Participants are children of 7 to 12 years old who meet the diagnostic criteria for an autism spectrum disorder (including autistic disorder, Asperger’s syndrome, and pervasive developmental disorder not otherwise specified (PDD-NOS)), according to the *Diagnostic and Statistical Manual of Mental Disorders* (DSM) [2]. This diagnosis is based on multiple assessments, including both observations and parent interviews, psychiatric and (neuro-) psychological examinations by multiple experienced clinicians (psychiatrists, psychologists, and educationalists). Additional diagnostic information is obtained by the Social Responsiveness Scale (SRS) [22]. Children are excluded if their total score is not in the clinical range. All participants have an IQ score within the normal range (70 or above). Before joining the study, both parents give active informed consent.

### Procedure

Participants are recruited from the Bascule, an academic center for children and adolescent psychiatry in Amsterdam, the Netherlands. Approximately 270 children each year are referred to the center’s outpatient clinic for ASDs.

After obtaining informed consent from parents, children are randomized to an intervention or a waiting list control group. Importantly, children in both groups start their intervention 10 weeks after the moment of randomization. The children in the control group have their first assessment directly after the randomization, followed by a waiting period of 8 weeks. Their second assessment is one week prior to the start of the intervention. The children in the intervention group have their first assessment about 8 weeks after the moment of randomization, in the week directly prior to the start of their intervention. Their second assessment is immediately after the intervention. We collect follow-up data six months after ending the intervention.

### Randomization

Randomization takes place 9 to 10 weeks before the start of the intervention. An independent research colleague randomizes the children using a digital random number generator. The randomization outcome is shared with the primary investigator, who informs parents about the condition.

### Sample size

The sample size is based on the minimum effect size (Cohen’s *d* = 0.25) found in the intention-to-treat sample of the previous trial [12]. Based on an *α* of 0.05 and a power of 0.80, we need 40 subjects in each condition to demonstrate this effect size. The additional 20 participants allow for the analysis of the effects of the two moderator variables (social interactive style and disruptive behavior).

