Strengths of the study include its large sample size, allowing the examination of predictors and moderators of intervention effects, and the multi-informant design, including children, parents, and teachers. Moreover, specific conceptual and practical social behavior skills are assessed as outcomes and follow-up data will be collected six months after ending the intervention. The current intervention has been used in Dutch clinics for nearly two decades [23], while similar interventions are commonly used worldwide for children with ASD. Given the limited evidence for its effectiveness, a thorough evaluation is sorely needed.

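### The stated inputs do not give 40 children per arm: at Cohen's d = 0.25 that size has about 20% power, not 80%

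*Protocol article*

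**What the plan says.** The Sample size section of the protocol article rests on "the minimum effect size (Cohen’s *d* = 0.25) found in the intention-to-treat sample of the previous trial". From that effect and an α of 0.05 it concludes: "and a power of 0.80, we need 40 subjects in each condition to demonstrate this effect size". A further 20 children are added for the two moderator analyses, which gives the planned total of 100. The section gives no sidedness, pre-post correlation, covariate adjustment or dropout allowance.

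The Statistical analysis section plans analyses of variance comparing the two groups on change in conceptual and practical skills, with between-group Cohen's d as the effect size.

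The Background faults two earlier trials, of 27 and 40 participants, for small samples "resulting in insufficient power to detect subtle treatment effects". The Discussion says: "Strengths of the study include its large sample size".

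**The concern.** An effect of a quarter of a standard deviation is small, and 40 per arm is far below what a two-group comparison needs to detect it with 80% power. The section gives an effect, an α, a power and a resulting number, so the claim can be checked directly.

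The stated power tells the reader how to take a non-significant result. Someone who believes the trial had 80% power for d = 0.25 will read such a result as fair evidence that the intervention does not work. If the real power is near 20%, a true effect of the planning size would be missed about four times in five. The trial would then share the weakness that its Background finds in the earlier trials.

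**Working it through.** **Inputs.** From the Sample size section: d = 0.25, α = 0.05, power 0.80, 40 per condition. From the Abstract: 100 children in total, taken as 50 per arm. Sidedness is not stated. Two-sided is taken as the convention, and one-sided is also tried.

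**1. Attempt to reproduce the plan's figure.** For two equal groups,

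n per arm = 2(z₁₋α/₂ + z₁₋β)² / d² = 2(1.960 + 0.842)² / 0.25² = 2 × 7.849 / 0.0625 ≈ 251.2, so 252.

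The noncentral t gives 252.1, so 253 per arm. The stated 40 is not reproduced; the requirement is about 6.3 times larger (253/40).

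**2. Power at the stated size.** The noncentrality is d√(n/2) = 0.25 × √20 = 1.118, so power ≈ Φ(1.118 − 1.960) = Φ(−0.842) = 0.20. By the noncentral t it is 19.7% at 40 per arm and 23.6% at 50.

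The value −0.842 is the normal quantile for a probability of 0.20. So 40 per arm is almost exactly the size that the formula returns for power 0.20: 2(1.960 − 0.842)² / 0.0625 ≈ 40. Power and type II error may have been exchanged, but the article does not show how the number arose.

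**3. Detectable effect at 80% power, two-sided.** (1.960 + 0.842) × √(2/n) gives 0.63 at n = 40 and 0.56 at n = 50. The noncentral t gives 0.634 and 0.566.

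**4. Other readings of the same inputs.**
- One-sided α of 0.05: 199 per arm needed; power at 40 per arm 29.6%, at 50 per arm 34.3%.
- 0.25 read as Cohen's f (d = 0.50): 64 per arm two-sided, 51 one-sided.
- Paired test at d = 0.25: 128 two-sided, 101 one-sided.

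None gives 40.

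**5. Gain from analysing change.** If d is on the raw-score standard deviation and the pre-post correlation is ρ, the effect becomes 0.25/√(2(1 − ρ)) for change scores, or 0.25/√(1 − ρ²) with baseline adjustment. Two-sided power at 40 per arm:

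| ρ | Change score | Baseline-adjusted |
|---|---|---|
| 0.5 | 20% | 25% |
| 0.7 | 30% | 34% |
| 0.8 | 42% | 45% |
| 0.9 | 70% | 72% |
| 0.92 | 79% | 80% |
| 0.95 | 94% | 94% |

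For 80% power at 40 per arm the effect must reach 0.634. For change scores, 2(1 − ρ) = (0.25/0.634)² ≈ 0.155, so ρ ≈ 0.92. With baseline adjustment, 1 − ρ² ≈ 0.155 and again ρ ≈ 0.92. One-sided, about 0.90 is enough. If d is already on the change-score standard deviation, the correlation brings no gain and the power stays at 19.7%.

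**6. Repeated-measures interaction.** With two groups and two time points, λ = f² × N × 2/(1 − ρ). Setting f = d/2 = 0.125 with ρ = 0.7 gives 78 children in total, and 81% power at 80. In this layout, however, the between-group difference in change is 4f standard deviations, so f = 0.125 means 0.5, twice the planning effect. The matching value is f = 0.25/4 = 0.0625, which needs 304 in total at ρ = 0.7 and has 30% power at 80.

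**The case against.** The strongest reply is that the 20% figure is conditional. The Sample size section states neither sidedness nor the scale of d, and the previous trial that supplied d is not at hand. The planned analysis is of change, so a high pre-post correlation could raise the power a good deal. The ToM test, the first primary outcome listed, has a reported test-retest intraclass correlation of 0.80 to 0.99, a range that contains 0.92. A journal article may also leave the test family and the assumed correlation to the full protocol.

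Part of this stands: the power should be given as a range if d is on the raw-score scale. It does not rescue the sentence. The section does not invoke the intraclass correlation, which concerns one of several primary outcomes and at its lower end gives only 42% to 45% power. The LEAS-C, also primary, has a reported internal consistency of 0.64 to 0.71. Internal consistency is not a pre-post correlation, so the inference is indirect; taken as a rough ceiling on it, that range gives about 26% to 35% power. No retest figure is given for the SSQ or the SSB questionnaire.

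Two smaller objections are fair. The Discussion ties its remark on sample size to the study of predictors and moderators, so it is not a direct claim about d = 0.25. Confidence intervals may already be planned in an analysis plan that is not shown. Neither affects the arithmetic.

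**Conclusion.** The concern holds. The stated inputs lead to about 253 children per arm two-sided, or 199 one-sided. Two-sided power at d = 0.25 is 19.7% with 40 per arm and 23.6% with 50, so the extra 20 children do not repair the shortfall.

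The figures near 20% assume two-sided testing and d on the standard deviation of the analysed score. On the raw-score scale, power at 40 per arm runs from 20% at a pre-post correlation of 0.5 to 79% at 0.92. Only an unstated correlation of about 0.92 (0.90 one-sided) supports the claim, and the article gives no ground for it across the primary outcomes.

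No allowance is made here for dropout, for delivery in groups of five or six children, or for several primary outcomes. These would lower power further, but the conclusion does not need them.

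The planned tests remain valid. The stated power is wrong, and it must be corrected because it is the only justification given for the sample size.

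**What to change.** Correct the Sample size section and leave enrolment as planned; the Trial status section reports that 80% of participants are already included.

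- Remove the claim that 40 per arm detects d = 0.25 with 80% power.
- State that, two-sided at α = 0.05 and before any dropout, 50 per arm has 80% power for d of about 0.57 and about 24% power for d = 0.25.
- State the sidedness and the standard deviation to which d refers. If the calculation rests on change scores or baseline adjustment, give the assumed pre-post correlation for each outcome, its source and the resulting detectable effect.
- Report each between-group effect as an estimate with a 95% confidence interval, so that a non-significant result is not read as no effect.
- Bring the Discussion's remarks on the adequacy of the sample into line with these figures.

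The cost is wording only. The stated power becomes less favourable; design, enrolment and planned tests do not change.

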## Discussion

This study will examine the effectiveness of a theory of mind intervention for children with ASD. By comparing a randomized intervention and a waiting list control group we aim to determine whether this widely used short intervention is effective in promoting children’s conceptual and practical social skills. It is hypothesized that the intervention will increase daily life social skills of the participants, in comparison with the waiting list control group [12,15]. However, by using more sensitive measures of practical daily life social skills we also expect the intervention group to improve in their parent- and teacher-reported social behavior.

Besides determining whether this intervention is effective, a second important goal is to assess for whom this intervention is most effective. By including an adequately large sample, it is possible to address potential origins of individual differences in response to the intervention. Specifically, we aim to determine the impact of social interaction style and disruptive behavior on the intervention effect. The phenotypical heterogeneity of children with ASD requires individual care, tuned to the specific needs of each individual. By determining the influence of individual characteristics of the child on the efficacy of the current intervention we contribute to this need.

Scheeren *et al*. [17] studied social interaction styles of children and adolescents with ASD and concluded that children with specific Wing subtype interaction styles may profit from different elements of the therapy. For example, children with an active-but-odd interaction style might be expected to profit more from interventions emphasizing conceptual understanding, while children with passive or aloof styles might profit more from interventions emphasizing motivation for social interaction. Antshel *et al*. [19] highlighted the negative impact of disruptive behavior on the effectiveness of a social skills intervention in children with ASD. In this study, comorbid disruptive behavior probably also prevents children from taking full advantage of the intervention.

A limitation of the current design is the absence of diagnostic instruments, such as the Autism Diagnostic Observation Scale (ADOS [37]) and the ADI-R (Autism Diagnostic Interview-Revised [38]). However, we do rely on an extensive clinical assessment (see Participants section), and administer the Social Responsiveness Scale [22] to validate the diagnosis.

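### The protocol presents 100 children as enough for the two moderator analyses; neither its sample-size premise nor the design supports this, except possibly for a continuous moderator

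*Protocol article*

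**What the plan says.** The Abstract makes finding the subgroups that profit most the second objective. The Sample size section takes d = 0.25 as the planning effect: "Based on an *α* of 0.05 and a power of 0.80", "we need 40 subjects in each condition to demonstrate this effect size". The step from 80 to 100 is explained in one sentence: "The additional 20 participants allow for the analysis of the effects of the two moderator variables", meaning social interaction style (SIS) and disruptive behavior (DB). No interaction effect size, power or detectable difference is given.

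The Discussion goes further. It says "By including an adequately large sample, it is possible to address potential origins of individual differences in response to the intervention", and it lists the sample as a strength: "Strengths of the study include its large sample size, allowing the examination of predictors and moderators of intervention effects".

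Statistical analysis plans Group × SIS and Group × DB terms in multiple regressions on change, controlling for autism severity and intellectual ability. The Wing Subgroups Questionnaire (WSQ) assigns one of three subtypes but also collects seven-point ratings. The Disruptive Behavior Disorders scale (DBD) is a 42-item rating scale. The article does not say whether either moderator enters as categories or as a score.

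**The concern.** With a balanced two-level moderator, the interaction contrast has twice the standard error of the overall treatment effect. An interaction as large as the main effect therefore needs four times the sample. The protocol adds a quarter (20 to 80).

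If the sample is described as adequate when it is not, real moderation may be missed. A non-significant interaction could then be taken as evidence that the intervention works equally well for everyone, and an isolated significant one is likely to be exaggerated. The Discussion intends the moderator results to inform care tuned to the individual child, so how firmly they can be read matters.

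**Working it through.** **Inputs from the protocol.** d = 0.25, α = 0.05, power 0.80, 40 per condition (Sample size); 100 children in total (Abstract, Methods).

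**Assumptions.** 1:1 allocation; two-sided testing (sidedness is not stated); subtype shares of 50:50, 20:80, equal thirds or 20:30:50; an interaction of 0.25, equal to the planned main effect; no dropout.

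**Step 1: the protocol's own figure.** With outcome SD 1, n per arm = 2 × (2.80/0.25)² ≈ 252 (198 one-sided), not 40. Power at 40 per arm is 20%, and at 50 per arm 24%. For 40 per arm to give 80%, the residual SD must be 0.25 / (2.80 × √(2/40)) = 0.25/0.626 ≈ 0.40. That corresponds to a pre-post correlation of √(1 − 0.40²) ≈ 0.92 under baseline adjustment, or 1 − 0.40²/2 = 0.92 for change scores. The protocol states no such input.

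**Step 2: standard error of the interaction at N = 100, SD 1.**
- Binary moderator with share q: SE = 2/√(N·q·(1−q)). This is 0.40 for 50:50 and 0.50 for 20:80.
- Continuous moderator, per moderator SD: SE = 2/√N = 0.20.
- Three subtypes: 2-df F test with noncentrality Σ(N·pₖ/4)(δₖ − δ̄)², where pₖ is the subtype share, δₖ the treatment effect in that subtype and δ̄ its weighted mean. The effects span 0.25.

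Under the protocol's premise each SE is multiplied by 0.40.

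**Step 3: power for an interaction of 0.25 at N = 100.**

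| Moderator | No variance reduction | Protocol's premise (residual SD 0.40) |
|---|---|---|
| Binary 50:50 | 0.25/0.40 = 0.625 → 9.6% | 35% |
| Binary 20:80 | 0.25/0.50 = 0.50 → 7.9% | 24% |
| Three subtypes, 2 df | 7-8% | 19-26% |
| Continuous, per SD | 0.25/0.20 = 1.25 → 24% | 88% |

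The last row is not directly comparable with the others. A 50:50 indicator has SD 0.5, so 0.25 per SD is a difference of 0.50 between the halves, and 0.50/0.40 = 1.25 gives the same 24%.

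**Step 4: what the extra 20 children buy.** With a 50:50 moderator, power moves from 8.6% to 9.6%, or from 29% to 35% under the premise. With a continuous moderator it moves from 20% to 24%, or from 80% to 88%. For 80% power with a 50:50 moderator, the premise itself requires 4 × 80 = 320 children.

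**Step 5: detectable interaction at N = 100, 80% power.** Without variance reduction: 2.80 × 0.20 = 0.56 SD per moderator SD, or 2.80 × 0.40 = 1.12 SD between two equal subgroups. Under the premise: 0.40 × 0.56 ≈ 0.22 and 0.40 × 1.12 ≈ 0.45.

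**Step 6: continuous score or split.** For a normally distributed moderator with a linear effect, a median split keeps √(2/π) ≈ 0.80 of the expected test statistic: 1.25 falls to about 1.00, and power from 24% to about 17%.

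**The case against.** The best defence has four parts.

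- **Saying that a sample allows an analysis promises no power.** This is true of the Sample size sentence alone. The Discussion, however, calls the sample adequately large and counts its size as a strength for moderators. That is an adequacy claim, and it can be checked.
- **Low power figures depend on ignoring variance reduction.** This stands as a limit. Analysis of change with covariates will reduce the residual SD by an unknown amount. If covariates explained 30% of the variance, power would be about 12% (50:50) to 32% (continuous). The retest coefficient of 0.80-0.99 in the Measures section belongs to the ToM test alone and is not used in the sample-size text.
- **The moderators may already be planned as continuous.** This is possible, since regression is specified and both instruments yield ratings. On the protocol's premise a continuous moderator would then be adequate. The fourfold rule applies to a balanced binary moderator only: per SD, a continuous moderator has the same standard error as the main effect.
- **The root fault is the main-effect calculation.** Largely so, and the two belong together. Even if that calculation were right, the subgroup contrasts would still reach only about 35%.

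Two stronger inferences should be resisted. A reader might conclude that moderator power simply is 8-24%. That range assumes SD 1, rests on assumed splits and mixes subgroup differences with per-SD slopes. A reader might also infer that continuous scoring halves the standard error. That compares one moderator SD with a contrast spanning two; the like-for-like loss from a median split is about 20% of the test statistic.

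The Background also says that "moderating and mediating variables are studied by examining the influence of social interaction style", although no mediation model appears in the article. That is loose wording, and a model could sit in the unseen analysis plan, as could the handling of multiple interaction tests. Neither is counted here.

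**Conclusion.** The point holds: 100 children are presented as adequate for the moderator objective, and the design does not support that. For categorical moderators, power for an interaction as large as the planned main effect is at most about 35% even if the protocol's premise is granted, and about 7-10% without variance reduction. For a single continuous moderator it lies between about 24% and 88% per SD, depending on a pre-post correlation that the protocol does not state.

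These figures rest on two-sided 5% tests, equal arms, assumed subtype shares and complete data. Dropout or a multiplicity correction would lower them. The documents do not show that the moderator analyses are worthless, or that a null result will be misreported. They show an adequacy claim without a basis.

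**What to change.** 1. In Sample size and both Discussion paragraphs, replace the adequacy statements with the interaction detectable at N = 100. With no variance reduction this is about 0.56 SD per moderator SD, or 1.12 SD between two equal subgroups. State the assumptions, and if a pre-post correlation is relied on, give it and its source.
2. Label the Group × SIS and Group × DB analyses exploratory.
3. Report interaction estimates with 95% confidence intervals, and draw no conclusion of absent moderation from p > 0.05.
4. State that the DBD and the WSQ subtype scores enter as continuous variables, which avoids the loss of about 20% of the test statistic from a median split.
5. Correct the main-effect calculation in the same section at the same time, since d = 0.25 needs about 252 per arm without variance reduction.

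Trial status reports 80% of participants already included, so these are changes of wording and analysis specification using data already being collected. The price is a weaker claim for the second objective.
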